## Abstract

**Background:**

Low grade chronic inflammation is observed in patients with type 2 diabetes mellitus (T2DM). Endotoxin derived from gut bacteria may act as a potent inflammatory stimulant. Probiotics, which are believed to contain health promoting live microorganisms, may influence circulating endotoxin levels. Ingestion of live probiotic cultures may alter gut microbiota in a beneficial manner to reduce inflammation; no information is available whether or not they do so in patients with T2DM. Therefore, the aim of this study is to characterize the beneficial effects of probiotics on circulating endotoxin levels and other biomarkers related to systemic low-grade inflammation in patients with T2DM.

**Methods:**

One hundred and twenty consenting adult Saudi T2DM patients (naïve or newly diagnosed and without co-morbidities) will be enrolled in this clinical trial and randomized to receive daily placebo or probiotics (Ecologic®Barrier) for 26 weeks in a double-blind manner. Inflammatory and metabolic markers will be measured and fecal samples analyzed. Measurements/samples will be obtained at baseline and after 4, 8, 12/13 and 26 weeks of treatment.

**Discussion:**

It is expected that the probiotic product will induce beneficial changes in gut microbiota, reduce the systemic inflammatory state through altering systemic endotoxin levels and, as such, reduce the systemic inflammatory response observed in T2DM subjects.

**Trial registration:**

ClinicalTrials.gov Identifier: NCT01765517

## Background

The human gastrointestinal tract contains bacteria, archaea and eukarya. In particular, bacteria living in the gut achieve the highest cell density recorded for any ecosystem [1]. However, gut microbiota does not exist independently and interacts at several levels in the functions of the body [1]. Specifically, gut microbiota can influence intestinal peristalsis [2], but also affects the expression of various host genes that regulate nutrient uptake, metabolism, angiogenesis, mucosal barrier function, the development of the enteric nervous system and maturation of mucosal immunity [3]. Interestingly it appears that fragments of Gram negative bacteria derived from the gut (endotoxin) can cross the intestinal mucosa to enter the circulation, and may represent an important mediator of low-grade systemic inflammation influenced by the host's own gut microbiota and metabolic state. Previous studies have shown that low levels of endotoxin can enter the blood circulatory system, which may stimulate an innate immune response from adipose tissue, liver and skeletal muscle, leading to production of pro-inflammatory cytokines [4-9]. Endotoxin has been shown to act as a mediator of inflammation in liver disease [10,11], whilst cross-sectional and longitudinal studies have indicated that a reduction in circulating endotoxin leads to a reduction in inflammatory cytokines and inflammatory response [12-15]. Furthermore, abnormal alterations in diet have a profound influence on human endotoxin circulation, but more so for patients with type 2 diabetes mellitus (T2DM) [16]. It makes sense that manipulation of diet to normalize the gut microflora and metabolic functions has been the mainstay management for most chronic diseases. In fact, a well-controlled diet is a major non-pharmacologic option for the prevention of T2DM [17,18]. As such, influencing the gut microbiota with the addition of probiotics may affect the systemic effects of endotoxin and represent a new and enhanced mechanism to treat low-grade chronic inflammatory conditions, such as seen in T2DM. The present study proposes to test the hypothesis that probiotics will alter the gut microbiota sufficiently to reduce systemic endotoxins and the resulting inflammation in subjects with T2DM, thus offering an additional intervention to treat these patients. To achieve this, 120 consenting adult Saudi T2DM patients without co-morbidities will be enrolled in this clinical trial and randomized to receive twice-daily placebo or probiotics for 26 weeks in a double-blind manner. Glycemic and inflammatory markers will be measured at baseline and at weeks 8, 12 and 26. The study will specifically explore the effects of probiotics on endotoxin levels in patients with DMT2 and relate them to the circulating levels of inflammatory cytokines.

## Methods

### Design

In this 26-week, single-center, double-blind, randomized, placebo-controlled study, 60 patients with T2DM will be treated with probiotics and 60 will be treated with placebo. Interventions will be performed at weeks 0, 4, 8, 12 and 26 in all subjects. Patients allocated to the probiotics group will receive two sachets with 2 g freeze-dried powder of the probiotic mixture Ecologic®Barrier daily (Winclove probiotics, the Netherlands). Ecologic®Barrier (2.5 × 10^9^ cfu/gram) contains the following bacterial strains: *Bifidobacterium bifidum* W23, *Bifidobacterium lactis* W52, *Lactobacillus acidophilus* W37, *Lactobacillus brevis* W63, *Lactobacillus casei* W56, *Lactobacillus salivarius* W24, *Lactococcus lactis* W19 and *Lactococcus lactis* W58. Participants in the placebo group will receive the placebo consisting of the carrier of the probiotic product, that is maize starch and maltodextrins. The placebo is indistinguishable in color, smell and taste from the probiotic sachets, but contains no bacteria.

### Recruitment of patients

Recruitment of patients to this study will be made possible by collaboration with primary care centers throughout Riyadh and the Biomarkers Research Program, College of Science, King Saud University.

### Ethical approval

The study protocol has been approved by the ethics committee of the College of Science, King Saud University, Riyadh, Saudi Arabia.

### Inclusion criteria

•Stable and well controlled T2DM (glycosylated hemoglobin (HbA1c) < 7.5% and no change in oral anti-diabetic medications during the last 6 months)

•Age 20 to 75 years

•Provision of written informed consent

### Exclusion criteria

•Chronic gastrointestinal disease (except irritable bowel syndrome)

•Systemic antibiotics within 6 weeks before inclusion

•Use of probiotics within 3 months before inclusion

•Regular intake of insulin or insulin analogs, antibiotics or probiotics, antacids, H2-receptor blockers, proton pump inhibitors, loperamide, cholestryramine, ω3-unsaturated fatty acid supplements, fibrates, corticosteroids or sex steroids

•Daily alcohol consumption > 30 g

•Significant immunodeficiency

•Known cardiac valvular disease

•Breast-feeding or pregnancy

•Non-Arab ethnicity

•Participation in another clinical trial within the last 6 months

•Legal incapability or mental incapacity to give consent.

### Allocation to treatment

After confirmation of eligibility and obtaining written informed consent, the patients will be given a unique subject number by the research nurse. The randomization (stratified for gender) will be performed by the probiotic company and the patients and clinicians at the primary care center will be blinded to the treatment received. The eligible patients will be allocated (1:1) to treatment for 26 weeks with either the probiotics supplement or placebo. Subjects will be instructed to:

•Ingest one sachet before breakfast and one sachet before going to bed, by mixing the powder in lukewarm water and drinking it.

•The sachets will be stored at room temperature.

### Data handling and record keeping

Case report forms (CRF) will be used to record data for all participants, and will be completed by the research nurse, who will also enter the data into an electronic database.

### Study schedule and location

After inclusion, all further treatments will be managed at the primary care center where the subject was recruited (see Table 1 for scheduled visits). A research nurse and a research dietician will be responsible for all contacts with patients. Doctors associated with the research team will be available if problems arise.

**Table 1 T1:** Schedule of visits

	**Pre-screening**	**Screening**	**Inclusion**	**Week**				
				**0**	**4**	**8**	**12**	**26**
Patient attends the health clinic		X		X		X	X	X
Telephone review					X			
Identification of eligible subjects	X							
Check eligibility		X						
Obtain informed consent			X					
Blood sampling				X		X		X
Stool sampling				X		X		X
Provision of test product				X		X	X	
Return of previously provided test product						X	X	X
Assessment of compliance and adverse events					X	X	X	X

### Acquisition of clinical data and assessment of compliance

•Medical history, including the presence of chronic diseases, regular medication, smoking and alcohol habits, will be recorded before inclusion.

•Nutritional habits will be assessed using a standardized 14-day recall questionnaire, which will be discussed with a dietician.

•Changes in medication during the study period will be recorded

•Anthropometric measurements will be made using standardized methods. Height will be measured at the start of treatment. Weight (in light clothing without shoes or items in pockets), waist circumference (measured as a horizontal plane at the level of the umbilicus) and hip circumference (measured as a horizontal plane at the level of the trochanter major) will be measured at the start and end of the treatment.

•Liver ultrasonography will be performed either at screening or at the start of treatment to determine the presence or absence of a bright liver indicative of steatosis. Patients with fatty liver and liver transaminases >1.5 × the upper limit of normal will be offered referral to a hepatologist.

•Compliance will be monitored at weeks 4, 8, 12 and 26. Patients will bring their previously received sachets to the primary care center to calculate the mean number of sachets used per day.

### Acquisition of routine biochemical data and biological samples

•Blood samples obtained will be analyzed at the Biomarkers Research Program to measure glucose, HbA1c, insulin, C-peptide, total cholesterol, high-density lipoprotein cholesterol, low-density lipoprotein cholesterol, triglycerides, alanine aminotransferase and aspartate aminotransferase levels.

•Fasting blood samples will be collected at weeks 0, 8 and 26. Peripheral venous blood will be drawn into pyrogen-free tubes without any anticoagulant. The tubes will be immediately placed in ice, allowed to coagulate, and centrifuged (2500 ×*g* for 10 minutes at 4°C) within 2 hours of collection. Serum samples will be stored at −80°C until use. At least two 2-mL serum samples will be collected at each time-point.

•Stool samples will be obtained at the same time points as blood samples and stored in a plastic sealable bag to be handed over to the clinic. Once at the clinic, the samples will be divided, flash frozen, and stored at −80°C. Changes in gut microbiota will be profiled using signature-tagged sequencing (pyrosequencing) of amplified 16*S* rRNA genes followed by automated bioinformatics analysis. Targeted RT-PCR will also be used to examine bacterial species such as *Enterobacteria* and *Bifdobacteria* relative to the universal bacterial primer set. Pyrosequencing and RT-PCR will be performed in a sub-cohort (n = 15) of patients considering the final systemic findings. Samples will be retained for subsequent studies.

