### Statistical aspects

#### Sample size

Preliminary data indicate that serum endotoxin levels in T2DM patients are two to three times higher than in control subjects. We hypothesize that treatment with probiotics will reduce mean endotoxin levels by 25 to 30%, while no change will be seen in the placebo group. To obtain 80% power to demonstrate a statistically significant difference (two-sided *P*-value = 0.05) between the two treatments, 100 patients must be treated (50 patients per group). As we expect a dropout rate of 15%, we will include 120 patients in the study.

The sample size was calculated based on the estimated mean change during treatment (Δ-values) and corresponding standard deviation (SD) of the change. Since we have no repeated measurements of endotoxin in the same individuals, we need to estimate the SD for the change. Assuming that the correlation between 1 and 2 yields a measurement of 0.70, the SD for the Δ-value is 78% of the SD of separate measurements (Table 2). Table 3 shows the estimated sample size according to various assumptions of treatment effect and correlation between one and two measurements.

**Table 2 T2:** Standard deviation and correlation between measures

**SD for each measurement**	**Correlation between measures**	**SD of the Δ-value**
1	0.60	0.89
1	0.65	0.84
1	0.70	0.78
1	0.75	0.71
1	0.80	0.63

Δ-value, mean change; SD, standard deviation.

**Table 3 T3:** Sample size determination for endotoxin

**Endotoxin baseline (U/L)**	**Difference in Δ-value (probiotics –placebo)**	**SD for change (common for both treatments)**	**Correlation for 1 and 2 measurements**	**Sample size (total) 2-tailed α: 0.05 Power: 80%**	**Sample size (total) 2-tailed α: 0.05 Power: 90%**
10 (± 6)	−2	5.34	0.60	224	298
	−2	5.04	0.65	200	266
	−2	4.68	0.70	176	236
	−2	4.26	0.75	148	198
	−2	3.78	0.80	116	154
	−2.5	5.34	0.60	144	192
	−2.5	5.04	0.65	128	172
	−2.5	4.68	0.70	114	152
	**−2.5**	**4.26**	**0.75**	**96**	**128**
	−2.5	3.78	0.80	76	100
	**−3**	**5.34**	**0.60**	**100**	**134**
	−3	5.04	0.65	90	120
	−3	4.68	0.70	80	106
	−3	4.26	0.75	68	90
	−3	3.78	0.80	54	70
	−4	5.34	0.60	58	76
	−4	5.04	0.65	52	68
	−4	4.68	0.70	46	62
	−4	4.26	0.75	40	52
	−4	3.78	0.80	32	40

Δ-value, mean change; SD, standard deviation.

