
Taken together, the current evidence appears to support a role for the gut microbiota in the pathogenesis of diet-induced obesity and related metabolic disorders, which may be reversible with dietary and/or gut microbiota manipulation [50]. As the gut microbiota is the main source of endotoxin, treatment with probiotics may influence the circulating levels of endotoxin by altering the microbiota composition. To date, relatively few studies have examined the effects of endotoxin in metabolic diseases using probiotics. To the best of our knowledge, this hypothesis has not been tested except in a small study of patients with cirrhosis in which a 25% reduction in endotoxin was reported [1]. However, animal studies have revealed that treatment with probiotics may be beneficial in insulin-resistant states [2,37]. Probiotics also delay the onset of glucose intolerance in high-fructose-fed rats [3]. To expand on these earlier findings, the present study will explore the potential beneficial effects of probiotics on circulating endotoxin levels and other markers for systemic low-grade inflammation in patients with T2DM.

In summary, we expect that our findings will demonstrate that probiotics alter gut microbiota in T2DM and that, in theory, the alterations will be metabolically favorable with continued probiotic use. Since the efficacy of probiotics is directly linked to the type of strain, we will also be able to identify which strains used in the intervention are most beneficial for patients with T2DM. Further investigations, however, will be needed whether the efficacy of the probiotics used in this study can be extended to prevention levels. Regardless, our study will be the first to address this issue beyond classical inflammatory conditions. This will have a fundamental impact on how we should treat the inflammatory component of T2DM, particularly once the results are verified in a larger cohort of patients.

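### The 15 patients for microbiota sequencing appear to be chosen in view of the final systemic results, which can bias the arm contrast and distorts the correlation with endotoxin

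*Protocol article*

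**What the plan says.** The rule stands in the protocol article under Acquisition of routine biochemical data and biological samples: "Pyrosequencing and RT-PCR will be performed in a sub-cohort (n = 15) of patients considering the final systemic findings". No other section gives a different basis for choosing the 15.

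Stool collection itself is not restricted to a subset: "Stool samples will be obtained at the same time points as blood samples", that is at weeks 0, 8 and 26 according to the same section and Table 1. The samples are frozen and kept.

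The microbiota is the first link of the stated mechanism. The Background sets out to "test the hypothesis that probiotics will alter the gut microbiota sufficiently to reduce systemic endotoxins and the resulting inflammation in subjects with T2DM", and the Discussion says "we expect that our findings will demonstrate that probiotics alter gut microbiota in T2DM". The Limitations section also falls back on microbiota effects in case inflammatory markers do not move.

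**The concern.** Allocation is 1:1 and random, so a microbiota contrast between arms is fair in all patients, or in any subset chosen without regard to what happened after randomisation. A subset chosen in view of endotoxin or inflammatory results lacks that protection. If patients whose endotoxin fell also tend to show a particular microbiota change, choosing on endotoxin also chooses on microbiota. If the choice works differently in the two arms, it creates a microbiota difference that the product did not cause. Even where the arms are treated alike, picking patients at the ends of the endotoxin range makes the microbiota-endotoxin correlation look stronger than it is.

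At stake is the evidence for the mechanism, which would rest on 15 of 120 patients (15/120 = 12.5%). This is a rule that the article states, not a detail left to a fuller document.

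**Working it through.** **Inputs from the article.** Sub-cohort n = 15; allocation 1:1; 50 evaluable patients per arm; two-sided alpha 0.05; 80% power.

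**Assumptions, because the article does not state them.** A split of 8 probiotic and 7 placebo patients; the selection rule; the within-arm correlation rho between endotoxin change and microbiota change (0, 0.3 or 0.5). Both changes are standard normal, with no treatment effect on either.

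**The plan's own figures.** No derivation is given for n = 15, so there is nothing to reproduce. The endotoxin sample size does reproduce: n per arm = 2(1.96 + 0.84)² × 5.34² / 3² = 49.7, rounded up to 50, so 100 in total as stated. Nothing below touches that figure.

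**False-positive rate of a nominal 5% t-test on microbiota change, probiotic v placebo (4,000 to 6,000 simulated trials per cell):**

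| Rule for choosing the 15 | rho 0 | rho 0.3 | rho 0.5 |
|---|---|---|---|
| Random | 5.3% | 5.0% | 5.0% |
| Best responders in both arms | 5.0% | 5.9% | 5.7% |
| Best 15 pooled over arms | 4.8% | 5.8% | 4.6% |
| Best and worst mixed within each arm | 4.7% | 2.4% | 0.7% |
| Best probiotic v random placebo | 4.7% | 13% | 29 to 30% |
| Best probiotic v worst placebo | 4.7% | 40% | 85% |

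**Why the last two rows differ from the rest.** The bias in the contrast equals rho × (mean endotoxin z-score of the chosen probiotic patients − that of the chosen placebo patients). For best v random the simulated bias is −0.44 SD at rho 0.3 and −0.73 SD at rho 0.5, so the gap in z-scores is about −0.44/0.3 = −1.5. For best v worst the bias is −0.91 and −1.52 SD, a gap of about −0.91/0.3 = −3.0. With rules that treat the arms alike the gap is near 0, and so is the bias.

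**Correlation.** Taking the 8 lowest and 7 highest endotoxin changes over both arms raises the mean observed correlation from 0.3 to about 0.52, and from 0.5 to about 0.75. At rho 0 it stays at 0. The range-expansion formula agrees: r = rho·k / √(1 − rho² + rho²k²), where k is the ratio of the endotoxin SD in the chosen patients to that in all patients. A single k of about 1.95 gives 0.585/√1.252 = 0.52 and 0.975/√1.701 = 0.75.

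**What a fair draw can show.** With 8 v 7, 80% power needs a difference of about 1.57 SD. At the standardised effects planned for endotoxin (3/5.34 = 0.56 and 2.5/4.26 = 0.59), power is 17 to 18%.

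**The case against.** The sentence is loose. It could mean that the conduct or extent of sequencing, not the choice of individuals, depends on the overall result. It does not say that patients are ranked on endotoxin, still less ranked differently by arm. Rules that treat the arms alike leave the arm contrast at or below roughly its nominal error rate, so the large figures need an asymmetric rule that the article never states. Sampling extremes is also a legitimate design when the rule is known and the analysis allows for it. The trial is sized on endotoxin alone, and stored stool would allow an unbiased sample to be assayed later.

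Most of this stands, and it limits the point. It does not remove it. The reading that patients are chosen on results is the natural one. On the alternative reading, whether or how far the mechanism is examined still depends on the outcome. And with no rule stated, there is nothing to adjust for in the analysis.

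A reader might go further and infer that selection builds in an association even if the product does nothing, or that the microbiota data would be uninterpretable. The article does not support either. At rho 0 no rule inflates the contrast or creates a correlation, and the actual rule is unknown. A reader might also object that both arms are not expressly required in the sub-cohort, but that is detail a condensed article may leave to the full protocol.

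**Conclusion.** The concern holds in a limited form. As written, the choice of the 15 most naturally depends on post-treatment results. That can bias the between-arm microbiota contrast, and choosing endotoxin extremes overstates the microbiota-endotoxin correlation, provided the two changes are related within arms. The hypothesis that "probiotics will alter the gut microbiota sufficiently to reduce systemic endotoxins" presupposes such a relation.

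The size cannot be fixed from the article. At assumed correlations of 0.3 to 0.5 the false-positive rate runs from below 5% to 85% according to the rule, and an inflated rate requires the arms to be treated differently. These figures illustrate a range and are not estimates for this trial. The randomised endotoxin comparison and its sample size are unaffected, so this is a defect in the mechanistic part of the study and not in its main comparison. It is best settled before any systemic result is seen.

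**What to change.** Replace the sentence with:

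> The sub-cohort (n = 15, 8 and 7 per arm, or 16 with 8 per arm) will be drawn at random within arm and gender by someone independent of the investigators, from the randomised patients, with a pre-drawn random replacement order for missing stool samples. The list will be fixed before any systemic result is available and before unblinding.

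Drawing from all randomised patients matters: limiting the draw to those with a week-26 sample would itself select on a post-randomisation event. The replacement order does not remove that entirely, so the number of replacements by arm should be reported. Drawing within arm needs the allocation list, so the person who draws must stand outside the blinded team.

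Label the microbiota results exploratory, since even a fair 8 v 7 draw can detect only a very large difference, and soften the expectation in the Discussion that the findings will demonstrate a microbiota change.

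The cost is one sentence, a random draw, and at most one additional patient's assays. The downside is that responders can no longer be hand-picked for sequencing.

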### Subject withdrawal

Subjects may withdraw from the trial at any time at their own request, or they may be withdrawn at any time at the discretion of the investigator for safety, behavioral or administrative reasons. The subjects will also be withdrawn from the study in case of:

•Treatment with systemic antibiotics for more than 1 week during weeks 0 to 22

•Any use of systemic antibiotics during weeks 22 to 26

